## Abstract

**Background:**

Xylitol use is reported to be able to reduce dental plaque amount and cariogenic bacteria and, as a consequence, the caries increment. Only few data on the oral health of Ladakh’s population are available. The aim of the present protocol will be to record the caries prevalence of primary and permanent molars of schoolchildren living in Ladakh and to implement a school-based Xylitol programme, named the *Ca*ries *Pre*vention *X*ylitol in *Ch*ildren (CaPreXCh) trial, using chewing gums.

**Methods:**

The protocol is designed as a triple-blind randomized, controlled, parallel-group clinical trial in children aged 5–14 years. The study should have been carried out from August 2021 to August 2024 in Zanskar Valley (Ladakh), but the COVID-19 pandemic does not allow today to make predictions on the exact start. Participants will be randomly allocated into two groups: subjects who will receive a chewing gum with Xylitol (70% w/v) as only sweetener, and those who will receive a sugared chewing gum containing Maltitol (23% w/v). The subjects will be instructed to chew a total of 6 pellets for 5 min divided into 3 intakes a day (2 in the morning, 2 after the midday meal and 2 in the afternoon) for one school year. Clinical examination will comprise an oral examination in which caries index (ICDAS scores), bleeding on probing and plaque pH evaluation after sucrose challenge will be recorded at baseline (*t*_0_); the clinical examination will be repeated after 12 months since the beginning of the chewing gum administration period (*t*_1_), after another 12-month period (*t*_2_) and finally after further 12 months (*t*_3_) (24 months from the end of the chewing gum use). The primary outcome will be the caries increment measured both at enamel and dentinal levels on primary and permanent molars. Data analysis will be conducted through Kaplan-Meyer graphs to evaluate caries increment. A comparison of the methods will be carried out with Cox regression with shared frailty. The net caries increment for initial, moderate and severe caries levels, using ICDAS (Δ-initial, Δ-moderate and Δ-severe), will be calculated.

**Discussion:**

This trial will be the first trial conducted in India assessing the efficacy of a school-based caries preventive programme through the use of chewing gum containing only Xylitol as a sweetener. The findings could help strengthen the evidence for the efficacy of Xylitol use in community-based caries prevention programmes in children.

**Trial registration:**

Clinical trials.govNCT04420780. Registered on June 9, 2020

**Supplementary Information:**

The online version contains supplementary material available at 10.1186/s13063-021-05828-y.

## Introduction

Ladakh is a region administered by India, covering an area slightly larger than Croatia; it is part of the larger region of Kashmir and Jammu, which has been the subject of dispute between India, Pakistan and China since 1947. The Indian Government reports Ladakh to be one of the districts that are below health service and condition standards [1]. The complex terrain and the high altitude, above 9000 ft, is responsible for the cold weather, a limited diet, a limited availability of drinking water and the poor socioeconomic conditions, factors affecting the population’s wellbeing [2–4].

The Italian National Association of Dentists Foundation (ANDI Foundation) has among its main aims that of improving the quality of life of populations with socioeconomic inequalities in various parts of the world, as the population living in the Zanskar Valley of Ladakh. Dental care is currently limited to small dental clinics, as at the medical centre in Padum (CHC, community health centre). During summertime, when the valley is accessible, teams of volunteers from the Italian National Dentistry Association (ANDI) Foundation work as dentists at the Padum’s facility and promote oral health in schools.

Oral health data on the population living in Ladakh are poor. A recent survey performed on schoolchildren living in Ladakh showed that caries was almost ubiquitarian with only 10% of caries-free children [5]. Caries severity, in both primary and permanent dentitions, was statistically significantly related to gender, waist circumference, body mass index (BMI), oral hygiene frequency and self-reported chewing problems. An increasing relative risk for caries in permanent dentition compared to caries-free subjects was observed in children with a low BMI [5].

The frequent intake of fermentable carbohydrates with the diet favours a high plaque cariogenicity, increasing the possibility of demineralization of enamel and dentin; the acidic environment of the plaque in turn promotes the growth of cariogenic bacteria, further increasing the caries risk [6]. As a consequence, different preventive approaches of caries prevention have focused on the reduction of sugar intake and its replacement with non-fermentable sweeteners, such as Xylitol. Polyols were proposed as an anti-caries agent since the 1970s, delivered mostly through chewing gum. Xylitol-based caries prevention programmes have been carried out in children and adults, showing the capacity of the polyol in reducing caries risk factors and caries incidence [7–9]. An advantage of using Xylitol in caries prevention programmes is that it does not require specifically trained personnel for its administration, since it can be easily given both at home by parents and at school by teachers even in less served areas of the earth.

Although encouraging results were obtained in children in ten RCT studies, the quality of evidence was rated as very low [10], calling for the need of well-conducted and methodological sound trials. Moreover, the use of Xylitol for caries control is considered a preventive method that might encounter dietary-cultural obstacles, especially in countries where polyol and or chewing gum use are not frequently consumed, and this aspect needs also to be further investigated.

Recently, a chewing gum sweetened with Xylitol only was proposed. A preliminary study showed that this product is able to increase significantly the Xylitol concentration in saliva compared to the level obtained using a chewing gum containing different polyols. Furthermore, the chewing gum also demonstrated to have the capacity of reducing bacterial strains related to caries and periodontal disease [11].

The aim of the present protocol will be to register the caries prevalence of schoolchildren living in Ladakh and to implement a school-based Xylitol programme using chewing gums in order to reduce caries incidence.

## Methods

### Trial design

This is the third and final version of the protocol (edited on the 15th of May 2021). A superiority trial is designed to detect a difference between treatments as a triple-blind randomized, controlled, parallel-group clinical trial. Two groups will be compared: subjects who will receive a Xylitol chewing gum with the polyol as the only sweetener (70% w/v), and those who will receive sugared gum containing a 23% (w/v) Maltitol. The flowchart of the study design is displayed in Fig. 1.

**Fig. 1 Fig1:**
[figure not shown]
The flowchart of the study design

The investigation will have an experimental period of one school year (approximately 9 months in total). The study will gain the approval of all the schools’ authorities. Due to language problems and the low literacy rate of the population, parents’ or guardians’ verbal approval will be obtained for children’s participation.

The trial—Caries Prevention Xylitol in Children (CaPreXCh)—was registered with ClinicalTrial.gov (NCT04420780) and is currently in the no-recruiting phase. The Standard Protocol Items for Clinical Trials (SPIRIT) was used to guide the present protocol as detailed in online supplementary appendix (Additional file 1).

The study should have been carried out from August 2021 to August 2024 in Zanskar Valley (Ladakh), but due to the persistence of the COVID-19 pandemic, it is not possible to predict the real beginning of the trial.

### Participants, interventions and outcomes

#### Setting

The study will be conducted in the Zanskar Valley (Ladakh). School classes of subjects aged 5–14 years old will be randomly selected from a list of classes in the selected schools.

In 2018, the total schoolchildren population in the Zanskar Valley aged 5–17 years amounted to 2407 children.

#### Eligibility: inclusion and exclusion criteria

The inclusion criteria will consider the following:

a) To be 5–14 years old

b) To be in good general health

The exclusion criteria will consider the following:

a) Children who refuse to participate in the research; parents/guardians who refuse the participation of their children to the trial

b) Children who present systemic conditions or chronic diseases that require differentiated care and follow-up

#### Preliminary epidemiological survey

A team of four dentists received training to diagnose caries lesions using the WHO-DMFT index for permanent teeth and the dmft for primary teeth. The team received training, and inter-examiner reliability was assessed before the start of the study; sensitivity, specificity, percentage agreement and kappa statistics were recorded. Inter-examiner reliability ranged from 0.75 to 0.84 (K-Cohen) for sound teeth and from 0.82 to 0.88 for caries lesions. Intra-examiner reliability ranged from 0.82 to 0.90 for sound teeth and from 0.84 to 0.91 for caries lesions. Dental caries prevalence (dt/DT) and severity (number of lesions) were recorded for caries at the dentinal lesion level [12]. Every subject was examined using a plain mirror (Hahnenkratt, Königsbach, Germany) and the WHO CPI ballpoint probe (Asa-Dental, Milan, Italy), under standard light. No bitewing radiographs or fibre-optic trans-illumination were used.

An ad hoc prepared questionnaire assessed general health, eating habits, oral hygiene and the self-perception of oral conditions, based on previous surveys [12, 13]. The height (cm) and the weight (kg) were measured and the body mass index (BMI) was calculated. The waist circumference was also measured.

Caries was almost ubiquitarian with only 10.04% of caries-free children (dt/DT = 0). Caries severity, in both primary and permanent dentitions, was statistically significantly related to gender and waist circumference (*p* < 0.01). This preliminary epidemiological survey will allow to design the intervention trial.

### Interventions

After obtaining actual caries data, schools with similar numbers of schoolchildren (at least 300 subjects per school) will be selected for the preventive project. The participants will be randomized, taking as cluster the school class, allocating each class into one of the two groups of the study (Fig. 1):

(1) The first group (Xyl) will receive sugar-free gums containing 70% (w/v) Xylitol as the only sweetener

(2) The second group (Pol) will receive reduced sugared gums containing 23% (w/v) Maltitol

Both groups of children will receive a total of 6 pellets of chewing gum a day during a period of one school year (about 9 months). All chewing gums will be produced and supplied by Perfetti Van Melle SpA (Lainate, Italy). All types of chewing gums will weigh 1.4 g each and will be identical in colour, shape and taste.

#### Clinical examination

Clinical examination, coordinated by [name] as responsible of the coordinating centre, will comprise an oral examination (caries index, bleeding on probing recording) and an evaluation of plaque pH fluctuation after the sucrose challenge. Bleeding on probing will be used as a proxy of plaque presence, since there is a causal relationship between bleeding on probing and amount of plaque [13, 14].

The subjects will be examined using a mouth mirror, a ball-ended probe and artificial light. Caries registration will be performed with regard to the first and second primary, and first and second permanent, molars. The International Caries Detection and Assessment System (ICDAS) will be used to record caries at tooth level as initial, moderate or severe lesions, the number of filled teeth and the missing teeth for caries [15, 16]. Initial caries lesion can be defined as a primary lesion, which has not reached the stage of an established lesion with cavitation (ICDAS scores 1 and 2). Moderate caries lesions are defined as white or brown spot lesion with localized enamel breakdown or an underlying dentine shadow without visible dentine exposure (ICDAS scores 3 and 4). Extensive caries lesions are defined as a distinct cavity in opaque or discoloured enamel with visible dentine (ICDAS scores 5 and 6) [9, 15, 16]. The bleeding on probing score, as the percentage of periodontal site bleeding, will be registered in all subjects.

#### Plaque pH measurements

Interproximal plaque pH, as an interim indicator, will be evaluated using pH indicator strips [17, 18], which measure a pH value in the range of 4.0–7.0 (Spezialindikator, pH range 4.0–7.0; Merck, Darmstadt, Germany). The strips determine changes in plaque pH, discriminating differences at the level of 0.2–0.5 pH units, and they are easy to use. The strips will be cut into 4 pieces (approx. 2 mm in width) in order to get a strip that could be easily inserted into the interproximal space, held in situ for 10 s and its colour compared to the colour index scheme supplied by the manufacturer.

For each subject, 3 measurements will be carried out in 2 sites, between the 2nd premolar or the 2nd primary molar, if present, and the 1st molar right and left of the upper jaw. Measurements will be performed before and at 2, 5, 10, 15 and 20 min after a mouth rinse with 10% sucrose.

#### Calibration of the examiners

Four dentists will be trained and calibrated by a benchmark examiner. Baseline training will consist of a 1-day theoretical course, followed by an examination of extracted teeth, plus a session of photographs. After 2 days of the theoretical course, a clinical training will be performed. Twenty children will be examined and re-examined after 72 h. Inter-examiner reliability with the benchmark examiner will be evaluated using fixed-effects analysis of variance and intra-examiner reproducibility assessed as the percentage of agreement using Cohen’s kappa statistic [11].

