### Data collection, management, and analysis

The follow-up assessments will be performed by calibrated blinded dentists. The clinical data will be recorded on electronic sheets organized on PageMaker and then transferred into Microsoft Excel Software. The data management team is formed by two authors ([name], [name]). Data will be cleaned, deleting those revealing the participants’ identities, and they will be shared in a public repository at the moment of the submission of the manuscripts.

Data on caries will be recorded considering the tooth as the unit of analysis. The progression or change of status can be described with three modalities: 1—as the change from no caries stage to initial stage or to moderate stage or extensive; 2—as the change from initial stage to moderate or extensive stage; and 3—as the change from moderate stage to extensive stage. The net caries increment for initial, moderate and extensive caries levels, using ICDAS (Δ-initial, Δ-moderate and Δ-extensive), will be calculated in primary and permanent molars. Differences between groups in terms of caries increment will be evaluated using the nonparametric Mann–Whitney *U* test. Data analysis will be conducted through Kaplan–Meyer graphs to evaluate caries increment. A comparison of the methods will be carried out with Cox regression with shared frailty. The calculation of sensitivity, specificity and accuracy will consider the results obtained with the indices and the classification of caries lesion presence by the proposed reference standard. The cost-effectiveness ratio will also be verified, considering as effectiveness the prevention of the primary outcome. For all tests, two-tailed analyses will be used, considering a level of significance of 5%. The quality-adjusted life-year index (QALY) will be calculated to assess the value of the preventive intervention [22]. To determine QALYs, the utility value associated with a given state of health by the years lived in that state will be calculated. A year of life lived with no caries increment will be worth 1 QALY (1 year of life × 1 utility value) [22, 23]. Plans to promote participant retention and completion of follow-ups will be performed; a list of any outcome in participants who discontinue the treatment will be compiled and the data will be analysed, taking into account that living conditions in Ladakh do not allow for high mobility of the population. This will make participant retention a minor problem.

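### Agreement with the benchmark examiner is assessed by analysis of variance, which compares mean scores; no planned statistic would expose an examiner who is self-consistent but stages teeth differently from the benchmark

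*Protocol article*

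**What the plan says.** The calibration section of the protocol article assigns a different method to each of two checks.

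- Against the benchmark: "Inter-examiner reliability with the benchmark examiner will be evaluated using fixed-effects analysis of variance".
- Within examiner: "intra-examiner reproducibility assessed as the percentage of agreement using Cohen’s kappa statistic".

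The set-up is "Four dentists will be trained and calibrated by a benchmark examiner", and "Twenty children will be examined and re-examined after 72 h". No kappa, intraclass correlation or percentage agreement is named for the benchmark comparison.

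The measurement being calibrated is an ordinal stage on a tooth. Under Clinical examination, ICDAS "will be used to record caries at tooth level as initial, moderate or severe lesions", and initial lesions are codes 1 and 2. Under Data collection, management, and analysis, "Data on caries will be recorded considering the tooth as the unit of analysis", and an event is a change in the status of a single tooth. The same section relies on the calibration: "The follow-up assessments will be performed by calibrated blinded dentists".

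The preliminary survey did use kappa between examiners: "Inter-examiner reliability ranged from 0.75 to 0.84 (K-Cohen) for sound teeth", with 0.82 to 0.88 for caries lesions. Those figures belong to the WHO DMFT/dmft index, with caries recorded at the dentine level.

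**The concern.** A statistic for examiner agreement should answer one question: do two people give this tooth the same stage? The examiner effect in an analysis of variance asks whether their average scores differ. Over-scoring on some teeth and under-scoring on others cancel in an average. They do not cancel in an outcome that counts stage changes tooth by tooth.

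Four dentists score children at baseline and at three later visits. The article does not say whether the same dentist sees the same child each time. If the dentist changes, a lasting difference in how two dentists stage a tooth is recorded as a new lesion, a progression or a reversal. The examiners are blinded, so such error should fall on both arms alike and would tend to pull the treatment difference toward zero. The risk is greatest at the boundary between sound and initial lesions, which the trial counts and the survey's agreement exercise did not cover.

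**Working it through.** The plan gives no calibration result or threshold, so there is no figure of its own to reproduce. The check asks what each planned statistic can and cannot detect.

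**Inputs from the document.** Four examiners plus a benchmark; 20 children examined twice 72 hours apart; tooth-level ordinal ICDAS scores; a two-sided 5% level (stated for all tests, and assumed to cover this one).

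**Assumptions.** 8 molars per child, so 20 × 8 = 160 teeth. The main runs use code probabilities 0.35, 0.10, 0.15, 0.08, 0.07, 0.13, 0.12 for ICDAS 0 to 6. Three four-level distributions, from uniform to 60/20/12/8%, were tried as well. Kappa is linearly weighted unless stated otherwise.

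**Step 1: what the F-test responds to.** With tooth and examiner as factors, F = MS(examiner) / MS(error), and MS(examiner) depends only on differences between examiner means. If all examiners have the same score distribution, the null hypothesis of equal means is true. The test is then non-significant in about 95% of sessions, whatever the tooth-by-tooth agreement.

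**Step 2: an exact example.** Take 160 teeth, 40 at each of four levels (0 to 3), and let each examiner's scores be a cyclic shift of the benchmark's. Every mean is (0+1+2+3)/4 = 1.5, so F = 0 and p = 1.00. Yet no tooth is scored as the benchmark scored it. Unweighted kappa is (0 − 0.25)/(1 − 0.25) = −0.33. An examiner who repeats the same shift 72 hours later has perfect self-agreement. This is a construction, but it shows that neither planned statistic need react.

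**Step 3: random error.** Each examiner copies the benchmark with probability r and otherwise scores at random, with fresh errors at the repeat. Benchmark kappa is then r and repeat kappa is r². At r = 0.50 the repeat kappa is 0.25; at r = 0.90 it is 0.81.

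**Step 4: stable difference in staging.** Each examiner has a personal reading of each tooth that matches the benchmark with probability r, and reproduces that reading with probability q at each session. Repeat kappa is q² and benchmark kappa is r × q. Setting q² = 0.90 gives q = 0.949. Setting r × q = 0.50 gives r = 0.50/0.949 = 0.527.

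| Scenario | Kappa vs benchmark | Kappa vs own repeat | F-test non-significant |
|---|---|---|---|
| Random error, chance level | 0.00 | 0.00 | about 95% |
| Random error, moderate | 0.50 | 0.25 | about 95% |
| Random error, small | 0.90 | 0.81 | about 95% |
| Self-consistent, different staging | 0.50 | 0.90 | about 95% |

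The F-test column, from the two-way analysis, does not separate any of the rows. The repeat kappa separates the first three but looks excellent in the fourth. Only the kappa against the benchmark identifies the fourth.

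**Step 5: what the fourth row means per tooth.** Chance agreement under the assumed codes is the sum of squared probabilities: 0.1225 + 0.0100 + 0.0225 + 0.0064 + 0.0049 + 0.0169 + 0.0144 = 0.1976. Exact agreement is 0.50 + 0.50 × 0.1976 = 0.60, so examiner and benchmark differ on about 40% of teeth.

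**The case against.** **The two planned checks are complementary.** Analysis of variance picks up systematic over- or under-scoring, and the 72-hour kappa picks up random error. This largely stands. A reader might infer that examiners scoring close to chance could pass the whole calibration; step 3 shows they could not, because their repeat kappa would be poor. What remains is the self-consistent examiner with a similar mean and different staging. How common such examiners are is unknown.

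**Nobody is declared calibrated by the F-test.** Correct. The article states no pass rule, so it cannot be said that a non-significant F would count as a pass. The article nevertheless relies on calibrated dentists, and the only stated comparison with the benchmark does not measure tooth-level agreement.

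**An intraclass correlation may be meant.** Mean squares from a fixed-effects analysis of variance can yield one, and that does measure agreement. The article is condensed and cites a source for its method that is not available here. If this was the intention, naming the coefficient and its form settles the point. As written, the article names a method for this comparison, and that method is not an agreement measure.

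**The survey team already agreed well.** Its kappa of 0.75 to 0.88 is reassuring about training, but it does not extend to initial lesions.

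**The test might also fail good examiners.** A reader might infer that it condemns a trivial shift. With one examiner scoring one code high on 6% of teeth and all others perfect, a two-way analysis rejects in about 99% of sessions. Once 5 to 10% of teeth are scored at random, rejection falls to about 9 to 12%, and a one-way analysis rejects in 0%. This is not a general property and forms no part of the point.

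**Conclusion.** The point holds in a limited form. The method named for agreement with the benchmark compares means. The kappa that would measure tooth-level agreement is planned only within examiner. One type of examiner therefore escapes both checks: in simulation, kappa 0.50 against the benchmark, 0.90 against the own repeat, and a non-significant F-test in about 95% of sessions.

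The 95% follows from equal score distributions across examiners and does not depend on the particular distribution. The 0.50 and 0.90 are chosen to illustrate the gap; they are not estimates for these dentists.

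A reader might go on to infer that the trial's caries increments will be unreliable. The document does not support that. No misclassification rate can be derived from it, and loss of power was not estimated. Blinded error would be expected to dilute a difference rather than create one. This is a weakness in the evidence for calibration, cheap to remove because the trial is not yet recruiting.

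**What to change.** In the calibration section, replace the sentence on reliability with wording to this effect:

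> From the 20-child session, each examiner's ICDAS stages will be compared tooth by tooth with the benchmark's using weighted Cohen's kappa (weights stated), with simple kappa at the sound/initial cut-off. Intra-examiner kappa will be computed from the 72-hour repeat. An examiner below the pre-set minimum against the benchmark will be retrained and reassessed before scoring trial children. Analysis of variance will serve only as a supplementary check for systematic over- or under-scoring.

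An intraclass correlation is an acceptable alternative to weighted kappa if its form is stated. The investigators should set the minimum in advance; 0.75, the lower end of inter-examiner kappa reached in the survey, is one example.

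The change needs no extra children, visits or staff: it is a different calculation on data already planned. The one practical cost is that an examiner below the minimum repeats the training session.
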